### Adverse events

The safety analysis will be performed on all participants who will have received at least one Guilu Xian treatment.

Regular quality assurance monitoring will be carried out for any adverse effects and to ensure that the study is safe and in line with the implementation plan. This will also ensure that the data are accurately recorded and stored. Any serious adverse effects will be reported to the principal investigator with immediate effect. We will compensate the participants accordingly according to the “Regulation on the Handling of Medical Malpractice” in China.

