Traditional Chinese medicine has a significant effect on improving the quality of oocytes, improving the endometrial receptivity, increasing the clinical pregnancy rate, and reducing pregnancy-related complications. Tortoise deer erxian ointment, also known as tortoise deer erxian gum, was first recorded by Wang Sancai, a Chinese physician in the Ming Dynasty(1569). Guilu Xian reported the addition of turtle shell glue to the original “Guilu Erxian Ointment” and adjusted the dosage to strengthen the effect of nourishing yin and latent yang. The prescription is based on the tortoise shell glue and turtle shell glue as the main medicine, which functions in tonifying the kidney and as a nourishing essence and yin and latent yang. The application of deer horn glue is based on the fact that “those who are good at tonifying yin must seek yin in yang, then yin is born in yang, and the source of spring is not thirsty” [13]. This maximizes the tonifying effect in the balance of yin and yang. Therefore, Guilu Xian has the effect of tonifying the kidney essence, nourishing yin and latent yang, replenishing qi and nourishing spirit, and delaying aging. According to TCM theory, the pathogenesis of older women with low prognosis is deficient kidney essence, spleen qi deficiency, liver depression, and blood deficiency. “Tonifying the kidney, regulating the liver and invigorating the spleen” is the main treatment method, which corresponds to the tortoise deer fairy syndrome previously described. Recent studies have shown that TCM formula Guilu Erxian ointment has a good effect on the treatment of the reproductive system, and has an estrogenic effect [14–17]. However, there is no clear case on how to improve prognosis among older women. Therefore, there is necessary that a well-designed randomized controlled trial to confirm the effectiveness and safety of Guilu Xian in improving IVF-ET outcome in older women with low prognosis.

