### Trial design

This is a prospective, randomized, placebo-controlled, double-blind, superiority trial assigned in a 1:1 ratio. The study institutions were the Genetic and Reproductive Center of Traditional Chinese and Western Medicine, Affiliated Hospital of Shandong University of Traditional Chinese Medicine, the Second Affiliated Hospital of Shandong University of Traditional Chinese Medicine, and Jinan Central Hospital. The project leader regularly coordinates and communicates with each unit to understand the progress of the project and ensure the smooth progress of the project and the guarantee of quality. In order to ensure that there are enough participants, we will take measures such as providing free basic examinations, free drugs, and car allowance to better attract participants to join.

The inclusion criteria for this study will be patients aged between 35 and 42 years old, with insufficient ovarian reserve parameters (The POSEIDON criteria AFC < 5, AMH < 1.1 ng/mL) [18], and poor ovarian response (that is, the number of oocytes obtained after standard ovarian stimulation is less than 3). Patients should meet the diagnostic criteria of western medicine infertility, that is, women living without contraception for at least 12 months who are not pregnant are infertile [19].

The exclusion criteria are women with BMI ≥ 25 kg/m^2^; women who suffer from genetic diseases that are not suitable for childbearing as stipulated in the Maternal and Child Health Care Law; women with severe endometriosis, adenomyosis, and immune infertility; with untreated hydrosalpinx; with congenital or acquired abnormal development of the uterus and severe deformities of other reproductive organs; women with a history of endocrine dysfunction such as reproductive system tumor, thyroid dysfunction, and hyperprolactinemia; women receiving ovarian stimulation therapy or OCP in recent 3 months; women with a previous history of gynecological surgery such as the ovary; and all other contraindications of assisted reproductive technology.

The discontinuation criteria will be women who have adverse reactions such as nausea and obesity occurring during medication, women with no dominant follicular growth, early follicular ovulation, and no egg acquisition during ovarian stimulation. Three days after egg harvesting, the embryo was not formed.

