### Case registration and allocation

The clinicians being involved in the study will record the basic AFC and AMH values of the patients after obtaining informed consent from the participants. Upon meeting the inclusion criteria, the patients will be randomly distributed in groups with the order of registration, and the clinicians are responsible for recruiting patients in sequence and will use case questionnaires to record their identity, age, and other basic information.

The clinicians will give medication to participants within 3 days after screening. Data will be recorded on drug distribution and use, and timely reports provided to the clinicians on the drug dose and patients’ discomfort during the process.

This study will include 120 patients who will be recruited and randomly divided into two groups using the R language version 3.5.1: the elderly test group and the elderly control group. Sixty, patients will be treated with Guilu Xian and 60 with the placebo. The elderly and the experimental group will be treated with an antagonist, and the tortoise deer fairy and placebo will be administered from the third day of menstruation before IVF.

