### Intervention

The Guilu Xian/placebo will be given to the patients at 5 g three times daily from the third day of their menstruation period before IVF for 40 days (provided by the preparation room of Affiliated Hospital of Shandong University of Traditional Chinese Medicine, and the extraction procedure will be based on the standard of preparation room SOP). Drug composition: tortoise glue, turtle glue, antler glue, Chinese wolfberry, American ginseng, Cornus officinalis, Hawthorn seed, jujube.

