### Supervision and management

We have also established a Data Monitoring Committee (DMC). The DMC is composed of the director of the Department of Reproductive Center of Shandong Provincial Hospital of Traditional Chinese Medicine as the chairman and the heads of the other two study sites as independent members. It is the responsibility of the DMC to monitor data, assess adverse events and cases of abnormal liver and kidney function results post-intervention on a regular monthly basis, review the core trial process, conduct interim analyses (the interim analysis includes the evaluation of the patient's follicular growth status, the number of retrieved oocytes and the incidence of adverse events. If the incidence of events of early follicular ovulation and absence of follicles after stimulation is as high as 30%, or the incidence of adverse events is as high as 10%, the trial will be terminated and the reasons for this will be analyzed.), and discuss relevant protocol amendments.

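### The safety analysis set is defined by receipt of Guilu Xian, so as written it omits the placebo arm and leaves adverse events without a comparator

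*Protocol article*

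**What the plan says.** The Adverse events section of the protocol article states: "The safety analysis will be performed on all participants who will have received at least one Guilu Xian treatment". No other section defines a safety population.

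The surrounding text describes a two-arm, blinded comparison:

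- Trial design: "This is a prospective, randomized, placebo-controlled, double-blind, superiority trial assigned in a 1:1 ratio".
- Case registration and allocation: "Sixty, patients will be treated with Guilu Xian and 60 with the placebo".
- Intervention, where both arms are meant: "The Guilu Xian/placebo will be given to the patients at 5 g three times daily".
- Introduction, where the need for a randomised controlled trial is argued: "to confirm the effectiveness and safety of Guilu Xian in improving IVF-ET outcome in older women with low prognosis".

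Supervision and management has the Data Monitoring Committee "assess adverse events and cases of abnormal liver and kidney function results post-intervention on a regular monthly basis". It also sets a termination rule: if "the incidence of adverse events is as high as 10%, the trial will be terminated". Neither statement names an arm or describes a between-arm comparison.

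**The concern.** A safety set in a placebo-controlled trial is normally everyone who took any study medication, active or placebo. Here the criterion is receipt of the active product alone, which would exclude the placebo arm by definition.

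That matters more than usual in this setting. Under the section on ovarian stimulation, both groups receive gonadotropin, a GnRH antagonist and an hCG trigger, with progesterone after transfer. The Trial design section names nausea and obesity as reactions leading to discontinuation, and the monitoring committee looks at liver and kidney results. Events of these kinds could come from the background regimen as well as from the herbal product. The concurrent blinded placebo arm is what would tell the two apart.

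Without it, two errors are possible. Background IVF events could be charged to Guilu Xian, or a real excess could go unrecognised because there is nothing to measure it against.

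**Working it through.** No figure in the plan depends on this definition, so there is none to reproduce. The check is a comparison of the text, followed by a simple count and an illustration of what the controlled analysis would deliver.

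**1. Does Guilu Xian mean the active product only?**

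| Section | Usage |
|---|---|
| Randomization and blinding | Identifies Guilu Xian as the active drug and names placebo separately |
| Case registration and allocation | 60 to Guilu Xian, 60 to placebo |
| Placebo | Contrasts the placebo with Guilu Xian |
| Intervention | Names both products when both arms are meant |
| Patient compliance | Names only the product in a rule that must cover both arms |
| Adverse events | Names only Guilu Xian |

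The defining usage is the active product. The compliance rule is an exception and is taken up under the objection.

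**2. Does another section supply a two-arm safety set?**

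- Data analysis defines the full analysis set as all randomised patients, plus a protocol-compliant subset. These are not described as safety populations, and the one sentence on safety sets a different criterion.
- Data analysis also plans Fisher's exact test for ratios between the two groups. This is a general method and does not say which participants enter a safety comparison.
- Supervision and management covers monthly monitoring and a 10% adverse-event threshold, with no arm or denominator given. That is monitoring during the trial, not a final comparative analysis.

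So nothing elsewhere overrides the sentence.

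**3. How many participants are affected?**

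Planned enrolment is 60 + 60 = 120. The safety set as written holds at most 60. The fraction excluded is 60/120 = 50%.

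**4. What can a one-arm set estimate?**

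Let *b* be the incidence under the IVF regimen with placebo and *d* the change due to Guilu Xian. The active arm estimates *b* + *d*. The placebo arm estimates *b*. With the active arm alone, *d* is not identifiable at any sample size.

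**5. What would both arms give?**

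With *n* = 60 per arm and a common incidence *p*, the large-sample 95% CI half-width for the risk difference is 1.96 × √[2*p*(1 − *p*)/60]. The article gives no event rates, so *p* is assumed over a range:

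| Assumed *p* per arm | Calculation | Half-width |
|---|---|---|
| 5% | 1.96 × √(2 × 0.05 × 0.95/60) | ±7.8 percentage points |
| 10% | 1.96 × √(2 × 0.10 × 0.90/60) | ±10.7 percentage points |
| 20% | 1.96 × √(2 × 0.20 × 0.80/60) | ±14.3 percentage points |

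These intervals are wide, but they estimate the right quantity. The one-arm set gives no such interval. The figures take all 60 women per arm as having had at least one dose; fewer would widen them.

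**The case against.** The strongest reply is that the sentence is loose wording for study medication. The Patient compliance section defines the 70% threshold only in terms of taking the Guilu product, yet under double-blinding that rule has to apply to both arms. The Concomitant care section likewise restricts all subjects by reference to the effect of the ointment. The article therefore does sometimes use the product name for whatever the participant was given. This point stands as a reason to doubt that the authors meant to exclude placebo women. It does not settle the meaning, because the Intervention section shows that the two-arm wording was available and the safety sentence does not use it.

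Second, adverse events appear to be collected in both arms. Recording of discomfort and monitoring committee review are not limited by arm, and clinicians and patients stay blinded until the end of the study. This is correct, and it limits the defect to the analysis population. No data need be lost if the sentence is corrected before analysis.

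Third, the stated aim concerns IVF-ET outcome only, and the Outcome measurement section lists no safety endpoint. That is also true: safety is a purpose given in the Introduction, not a formal objective. But the article plans a safety analysis and fixes who is in it, so the definition needs to be right whatever the formal status of safety.

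Fourth, the choice of summary measure is often left to an analysis plan, which is not shown here. That is fair for the reporting details. It does not apply to the population, which the article states outright. The primary outcome, the full analysis set and the sample size are unaffected.

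**Conclusion.** The concern holds: the safety set is wrong as written. Taken literally, it excludes 60 of the 120 planned women, all of the placebo arm, and leaves an adverse-event rate with no comparator in a trial whose design provides one. From that set, no between-arm risk difference or confidence interval can be calculated for any event.

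This rests on reading Guilu Xian as the active product, which is how the Randomization and blinding section identifies it. If the authors meant study medication in general, the correction is a clarification. If they did not, it restores the controlled comparison. The sentence must be changed in either case, because an analysis plan that follows it would inherit a one-arm safety analysis. The precision figures depend on assumed event rates and serve only as illustration.

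**What to change.** Replace the sentence in the Adverse events section with a definition along these lines: the safety set comprises all randomised participants who took at least one dose of study medication (Guilu Xian or placebo), analysed by treatment received. Add that each type of adverse event, including abnormal liver and kidney results, is reported by arm with a risk difference and 95% confidence interval; this reporting detail may sit in the analysis plan instead.

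The cost is one sentence in the protocol. It needs no extra participants, visits or data collection, since events in placebo women appear to be recorded already. The change should be made and dated before unblinding.

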### Ethical approval and consent

This study has been approved by the Reproductive Medicine Ethics Committees of the Affiliated Hospital of Shandong University.

Clinicians will receive written informed consent from each patient participating in the study before the study commences. This study was approved by the Ethics Committee of the Reproductive and genetic Center of Integrated traditional Chinese and Western Medicine in Jinan City, Shandong Province, China.

## Discussion

Previous studies have confirmed that traditional Chinese medicine formula Guilu Erxian ointment is effective in the treatment of male impotence, semen abnormalities, female dysfunctional uterine bleeding, peri-menopausal osteoporosis, and other reproductive system diseases. A recent study found that Jiawei Guilu Erxian ointment effectively increased the number of elementary ovarian follicles in mice with primary ovarian insufficiency [22]. However, Guilu Xian treatment has not been reported in an older population of infertile women. Therefore, this prospective, multi-center, randomized double-blind clinical trial will investigate the effect of Guilu Xian, a traditional Chinese medicine formula on IVF-ET outcome in older women with low prognosis.

This study is a multi-center prospective clinical trial with certain limitations. The trial will not completely rule out clinical treatment bias. It will be difficult to guarantee that patients have similar backgrounds when comparing the two groups.

There is no current study to predict the impact of the Chinese Medicine Guiluxian on elderly infertile patients. Therefore, a prospective study is required to determine the feasibility and effectiveness of the turtle deer fairy.

### Protocol amendments

If major modifications are planned, such as inclusion criteria, exclusion criteria, and analysis of trial outcomes, we will notify the trial registration center and journal through the official website. For others such as investigators, trial participants, or regulators, we will notify them by telephone.

### Trial status

The trial was registered at the Chinese Clinical Trial Registry (ChiCTR) which is assigned to be the representative registry of China to join WHO ICTRP in 2007.

This trial is at version 1.3, 16 December 2019 (ChiTR).

The actual study start date was 1 July 2020 and the anticipated study end date is 31 December 2021. The recruitment start date was 15 October 2020; the anticipated recruitment end date is 31 January 2022.

### Data dissemination

The findings of this study will be widely disseminated through conference papers, research reports, and academic publications.
